**Methods:**

A prospective, randomized, controlled, single-blind, multicentre interventional trial is described. Weekly one-hour dietary counseling sessions promoting a WFPBD emphasizing vegetables, fruits, whole-grains, nuts, and legumes, omitting animal products, and limiting fat intake over a six-month duration will be implemented. Participants will be 70 age and sex-matched individuals experiencing active or treated “cured” leprosy and PNP, randomized to either intervention or control groups. Primary outcome measures include efficacy via visual analog scale, subjective questionnaire and objective quantitative sensory testing, as well as safety, tolerability, and harms of a WFPBD on PNP in leprosy. This study will be initiated after Research Ethics Board (REB) approval at all participating sites, and in advance of study initiation, the trial will be registered at ClinicalTrials.gov.

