### 2.2. Study objectives and hypothesis

The overall objective of this study is to demonstrate the effect of a dietary lifestyle intervention, specifically a WFPBD, on neuropathic pain variables in leprosy. It is hypothesized that patients may demonstrate a statistically significant improvement in sensory and motor neuropathy, as well as pain, on comprehensive questionnaires and objective QST and muscle testing both within and between groups at study end. Secondary objectives include contextualizing the significance of diet in the treatment of chronic leprosy sequelae by demonstrating high tolerability and a limited side effect profile alongside aforementioned improvements in neuropathic pain. It is hypothesized that a WFPBD has the potential to serve as a low-risk, low-cost, low-tech intervention for chronic neuropathic pain, improving function and reducing overall morbidity of leprosy.

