#### 2.4.2. Lifestyle counseling

Participants in the intervention group will be instructed to follow a WFPBD for 24 weeks. The study duration was chosen as a conservative estimate of comparable lifestyle-based interventional trials that demonstrated statistically significant improvements in diabetes-related neuropathy outcomes (18, 19). The diet will emphasize vegetables, fruits, whole-grains, nuts, and legumes, while omitting animal products, and limiting fat intake (Table 2). Selection of specific plant-based components may differ across study sites in concordance with local culinary preferences and cultural practices related to food. By tailoring the diet to the unique cultural diaspora affected by leprosy, many of which already endorse plant-based components, we seek to enhance adherence and acceptability to the diet overall. Likewise, current economic projections suggest that diets seeking to reduce animal products are more affordable than current standard diets across all socioeconomic levels – particularly due to inclusion of global staples such as tubers, beans, legumes, and rice – further enhancing accessibility (48–50). Participants will receive weekly support and guidance via 1 h counseling sessions with registered dieticians or the equivalent at each participating site. Sessions will be designed to disseminate comprehensive guidelines for following the WFPBD including culturally acceptable recipes and addressing concerns or knowledge gaps regarding the intervention. Participants in both the intervention group, and control group will be instructed to continue their respective leprosy therapeutics as prescribed throughout the duration of the study. Finally, dietary adherence will be measured via monthly random 24 h dietary recalls, and participants are free to withdraw at any point during the trial if they no longer wish to participate.

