#### 3.2.7. Safety, tolerability, harms, adherence

Additional considerations concerning the longstanding implementation of a WFPBD within this population will also be assessed at each counseling session. Data on safety via the number of adverse events, tolerability via drop-out rate, and emerging harms, against gold standard PNP therapeutics (or non-interventions, such as watchful waiting) will be collected and summarized. Dietary adherence reported as a proportionate yes/no will also be collected to ensure interventional feasibility. Based on the current landscape of the literature a WFPBD is expected to perform as well, if not better, than the current standard of care when considering implementation (19, 47, 55) (Figure 3).

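### Tolerability is measured only by drop-out rate, which misses people who stop the diet but stay in follow-up, counts losses unrelated to the diet, and so does not on its own support a claim of high tolerability

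*Protocol article*

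**What the plan says.** Section 3.2.7, which stands under the primary outcomes, gives each item its own measure: "Data on safety via the number of adverse events", then "tolerability via drop-out rate", then emerging harms. Nothing else in the article is attached to tolerability.

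Adherence is collected but serves a different purpose: "Dietary adherence reported as a proportionate yes/no will also be collected to ensure interventional feasibility". Section 2.4.2 gives the instrument: "dietary adherence will be measured via monthly random 24 h dietary recalls".

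The outcome carries weight. The Methods paragraph of the abstract includes it among the primary outcome measures ("as well as safety, tolerability, and harms of a WFPBD on PNP in leprosy"). Section 2.2 makes it part of the secondary objectives, to be met "by demonstrating high tolerability and a limited side effect profile". No numerical threshold is given.

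The article does not say what drop-out means. Section 2.4.2 says that "participants are free to withdraw at any point during the trial if they no longer wish to participate", and section 2.6.1 allows 14% for withdrawal and loss to follow-up combined. Both describe leaving the trial. No section says how someone who stops the diet but remains in follow-up is classed.

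**The concern.** Leaving a trial and stopping a diet are separate events. In a 24-week diet trial with no investigational product to return, someone can easily go back to their usual food and still attend the final visit. Scored by drop-out, that person tolerated the diet. Conversely, someone who moves away, or is lost for any reason unconnected with food, is scored as not tolerating it.

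What is at stake is the tolerability conclusion. It is listed with the primary outcomes and feeds the argument in section 2.2 that the diet is a low-risk option. A reader told that 86% tolerated the diet would take this as a statement about the diet, when it is a statement about attendance.

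Drop-out among controls has no bearing on tolerating the diet, so comparing drop-out between arms does not repair the measure.

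**Working it through.** **Inputs.** From section 2.6.1: about 60 evaluable participants, 14% withdrawal or loss to follow-up, about 70 in total, 35 per group. Two quantities are not in the article and are assumptions:
- *q*, the share of completers who have stopped the diet, varied from 0% to 30%;
- *f*, the share of drop-outs who left because of the diet, set at its two extremes, 0 and 1.

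**The plan's own figure.** 60 / (1 − 0.14) = 69.8, rounded up to 70, or 35 per group. This reproduces. Expected drop-outs per arm: 0.14 × 35 = 4.9, about 5.

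**What the stated measure reports.** Tolerating = 1 − 0.14 = 86%. Neither *q* nor *f* enters, so the reading is the same whatever they are.

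**Share still on the diet, if all drop-outs are taken as off it.** 0.86 × (1 − *q*):
- *q* = 0%: 86.0%
- *q* = 10%: 0.86 × 0.90 = 77.4%
- *q* = 20%: 0.86 × 0.80 = 68.8%
- *q* = 30%: 0.86 × 0.70 = 60.2%

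**Both directions of error.** Diet discontinuation = 0.14 × *f* + 0.86 × *q*, against a drop-out reading of 14%:

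| *q* (assumed) | *f* = 1 (all drop-out due to the diet) | *f* = 0 (none due to the diet) | Drop-out rate reads |
|---|---|---|---|
| 0% | 14.0% | 0.0% | 14% |
| 10% | 22.6% | 8.6% | 14% |
| 20% | 31.2% | 17.2% | 14% |
| 30% | 39.8% | 25.8% | 14% |

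With *f* = 1 the drop-out rate is never too high, and it is too low as soon as any completer stops. With *f* = 0 it is too high until *q* passes 0.14 / 0.86 = 16.3%, and too low beyond that. The article gives no figure for either quantity, so the sign of the error cannot be fixed in advance.

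**Precision.** With 5 of 35 dropping out (14.3%), the exact (Clopper-Pearson) 95% CI is 4.8% to 30.3%; equivalently, 30 of 35 retained gives 69.7% to 95.2%. This reflects an arm of 35 and applies to any proportion measured in it, so it does not favour one definition over another. It does show why an interval belongs beside the figure.

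**The case against.** The strongest reply is that little is lost. Adherence is measured monthly, reported as a proportion beside drop-out, and listed in section 2.6.2 among the categorical variables to be reported by group. Adverse events and harms are collected too. Someone who quits the diet and stays in the trial should therefore show up in the adherence result. This stands in part. A reader might infer that the trial cannot support any statement on tolerability; the article does not bear that out, because the other data could be read together with drop-out. It remains true that the measure assigned to tolerability excludes them, and that adherence is assigned to feasibility.

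A second reply is that drop-out is undefined in a condensed article and might mean leaving the diet programme, since section 3.2.7 speaks of assessment at counselling sessions. That is possible, and the study-exit reading is an inference. But the other uses in the article point to study exit, and the point concerns a measure that is stated, not detail left to a fuller document.

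A third reply is that the bias has no proven direction. This stands in full. A reader might infer that the diet will look better tolerated than it is; the article does not establish this, because all-cause drop-out also counts losses unrelated to the diet. Nor should a reader infer a predictable advantage from control-arm losses. Losing more controls would flatter the diet and losing fewer would do the opposite. Section 3.2.7 says only that the data will be collected and summarised, and section 2.6.2 does not name drop-out among the variables to be tested.

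Finally, stopping for any reason mixes intolerance with cost, access and culture, and a single 24 h recall cannot tell a lapse from stopping. Both points are fair and shape the fix.

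**Conclusion.** The concern holds in a limited form. Drop-out rate, read as leaving the trial, does not on its own support "demonstrating high tolerability and a limited side effect profile". It cannot see diet discontinuation among people who stay, and it counts departures that have nothing to do with the diet.

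At the planned 14% drop-out the measure reads 86% tolerating. Counting all drop-outs as off the diet, the share still on it falls from 86% to 60% as *q* goes from 0% to 30%. If no drop-out were due to the diet and no completer stopped, the same reading would instead overstate discontinuation by 14 percentage points.

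This rests on the study-exit reading of drop-out and on assumed values of *q* and *f*, which illustrate the range and are not forecasts. The 14% is itself a whole-trial planning allowance, not an expected rate for the diet arm. The measure should be changed, because the outcome is listed as primary and the means to measure it properly are largely in place.

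**What to change.** In section 3.2.7, define tolerability in the intervention arm as the proportion of those randomised who discontinue the diet by 24 weeks, either by leaving the study because of the diet or by stopping it while in follow-up. Report it for any reason and separately for intolerance, each with an exact 95% CI. Where the reason for leaving the study is unknown, show the result with those participants counted both ways.

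Identify stopping from the record of the weekly counselling sessions, with the monthly recalls as support, and add a short entry for the reason at those contacts.

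Report study drop-out by arm separately, under the name retention. Read both results beside adherence and adverse events. State that drop-out means leaving the study, if that is what is intended.

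The cost is one short added field, one definition and one table. No extra visits are needed. The reported tolerability may be lower than under the present measure.

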### 3.3. Secondary outcomes

#### 3.3.1. Anthropometrics, sleep quality, physical activity, and diabetes control

As a dietary lifestyle intervention can have a drastic effect on anthropometrics, height and weight will be measured at both baseline and at the end of the study and will be used to calculate body mass index (BMI) (Figure 3). Likewise, sleep quality has been associated with neuropathy severity, and must be monitored throughout the trial. The Pittsburgh Sleep Quality index is a validated questionnaire, widely used to assess sleep perturbation due to various etiologies. Participants can be assigned a maximum of 21 points indicating severe difficulties in all areas of sleep quality (67). The PSQI will be collected at baseline and at the end of the study. Self-reported physical activity will also be collected at such intervals using the International Physical Activity Questionnaire. The IPAQ includes 27-items designed to gauge the frequency and intensity of physical activity carried out in a 7-day period, encompassing occupational, transportation, housework, and leisure activities. It has been extensively tested and validated throughout 12 countries and has previously been utilized in assessing self-reported physical activity in both diabetes and leprosy cohorts (68–70). To avoid the potentially confounding effects of additional lifestyle levers, such as sleep quality and exercise, these assessments are paramount during downstream analysis. Lastly, in individuals experiencing a biochemical diabetes due to leprosy related corticosteroids, an assessment of diabetes control including duration of illness, therapeutics used, and insulin status will also be carried out to monitor any changes throughout the trial (Figure 3). Standard biochemistry, including serum cholesterol, triglycerides, hemoglobin-A1c, serum glucose, hepatic transaminases, creatinine, and basic micronutrient panel (e.g., serum ferritin, B12) will be taken to measure diabetes parameters and general physiological status. To better ascertain the relationship between the dietary lifestyle intervention and leprosy itself, neuropathy and neuropathic pain outcomes will be stratified by secondary outputs, with specific emphasis on diabetes status, and steroid use.

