### 2.6. Statistical analysis

#### 2.6.1. Sample size calculation

This is a novel RCT addressing the implications of a WFPBD on neuropathic outcomes in individuals with leprosy. This relationship has not been directly assessed in the current body of literature, however similar research questions have been assessed in individuals with diabetes mellitus. As such, the sample size calculation herein will utilize this literature as a proxy. The efficacy of a WFPBD diet on neuropathy in a diabetes cohort has been reported via the Michigan Neuropathy Screening Instrument (MNSI), including both subjective (questionnaire) and objective (physical assessment) measures. The sample size calculation was based on the MNSI questionnaire measurement as explicit details pertaining to the MNSI physical assessment were not provided. Specifically, both the type of QST utilized (vibration, perception, both, etc.) and the location the test was carried out (lesion, glove, stocking, etc.) were not mentioned. Therefore, the MNSI questionnaire was preferentially chosen as a proxy. Participants receiving the intervention reported a final mean MNSI questionnaire of 5.3 ± 2.5 compared to 7.1 ± 2.8 in the control group at study end (19). Using an opensource sample size calculator with two independent study groups, continuous endpoints, an alpha of 0.5 and 80% power, a final sample size of approximately 60 participants was ascertained (53, 54). This is a conservative estimate as source literature demonstrated a statistically significant effect on outcomes with a relatively low population of 34 individuals (19). Assuming high acceptability and a 14% withdrawal and/or loss to follow-up rate based on previous literature, a final sample size of ~70 individuals, 35 per group, will be needed to adequately power this trial (19, 47, 55, 56).

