#### 2.6.2. Continuous and categorical variables

Descriptive statistics including reported means ± standard deviation for continuous variables [questionnaires including MNSI-physical assessment, Neuropathy Total Symptom Score (NTSS), modified Medical Research Council Scale (mMRCS), Neuropathic Pain Symptom Inventory (NPSI), McGill Pain Questionnaire (MPQ), Pittsburgh Sleep Quality Index (PSQI), and International Physical Activity Questionnaire (IPAQ) summative scores, visual analog scale (VAS), anthropometrics, diabetes duration, hemoglobin A1c, and serum micronutrient levels] and proportions for categorical variables [number of adverse events, dietary adherence, insulin use, leprosy clinical status (according to the WHO and Ridley Jopling classification systems), frequency and prevalence of inflammatory leprosy reactions, corticosteroid use] will be reported by each study group (57). Between- and within-group comparisons will also be made for continuous variables using the Student’s *t*-test with reported *p*-values, and for categorical variables using the chi square or Fisher’s exact tests, reporting *p*-values with odds ratios and 95% confidence intervals. Statistics will also be reported for all time points including baseline, and end of study. Multivariate logistic regression adjusting for covariates [such as age, sex, PROGRESS+ factors (58, 59), level of physical activity, smoking status, alcohol consumption, comorbidities, diabetes status] and potential effect modifiers (such as change in weight over time, medication de-escalation over time) will be carried out to ascertain the impact of a WFPBD on PNP in leprosy patient sub-populations and under various conditions. All statistical analysis will be carried out using GraphPad Prism 8 (GraphPad, United States).

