### 3.4. Potential stratifiers/confounders

Beyond primary and secondary endpoints, potentially confounding variables will be collected and utilized for downstream data analysis including: (1) demographic data: age, sex, socioeconomic status [relative within country and absolute according to World Bank definitions (75)], occupation (considering level of manual work, repetitive tasks, and prolonged standing/walking/climbing), household membership (living alone vs. with family members), and education level; and (2) lifestyle-related information: level of physical activity (via the international physical activity questionnaire), tobacco and cannabis smoking and alcohol consumption habits (amount consumed/day), and environment (urban vs. rural; meters a.s.l.). Effect modifiers including weight loss over time and de-escalation of medication over time will also be considered. Considerations of intervention cost, feasibility, cultural acceptability, and adherence will also be collected and summarized in a thematic analysis (Figure 3).

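### The planned adjustment and stratification do not test whether the diet effect differs between sub-populations, and the named effect modifiers arise after randomisation

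*Protocol article*

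**What the plan says.** Two places in the protocol article deal with effects in sub-populations.

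- **Section 2.6.2** plans a multivariate logistic regression. Its adjustment list has two parts. The covariates include "level of physical activity, smoking status, alcohol consumption, comorbidities, diabetes status". The second part is "potential effect modifiers (such as change in weight over time, medication de-escalation over time". The purpose given to the model is "to ascertain the impact of a WFPBD on PNP in leprosy patient sub-populations and under various conditions".
- **Section 3.3.1** closes with the statement that "neuropathy and neuropathic pain outcomes will be stratified by secondary outputs, with specific emphasis on diabetes status, and steroid use". The aim given there is to understand better how the diet relates to leprosy itself.

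Section 3.4 returns to the modifiers only briefly: "Effect modifiers including weight loss over time and de-escalation of medication over time will also be considered".

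For continuous outcomes the only comparison named is the t-test: "Between- and within-group comparisons will also be made for continuous variables using the Student’s" *t*-test (section 2.6.2). Corticosteroid use appears in section 2.6.2 as a categorical variable to be reported. It is not named in the regression. Nowhere does the article describe a comparison of the diet effect between strata.

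**The concern.** Section 2.6.2 pairs a method with a purpose that the method does not serve. A covariate or modifier entered as a main effect leaves a single diet coefficient for everyone. That coefficient does not show whether the diet works differently in people with and without diabetes, or on and off steroids. Splitting the outcomes by stratum gives separate descriptions, but two separate results do not test the difference between them.

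A second problem lies in the modifiers that are named. Weight change and medication de-escalation happen during follow-up and may themselves be effects of the diet. Adjusting for them, or grouping by them, can remove part of the effect under study or compare groups that are no longer balanced by randomisation. The same holds for any secondary output measured at study end and used as a stratifier.

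At stake is how a subgroup pattern would be read. The rationale carries evidence from diabetic neuropathy over to leprosy, so a result seen in one diabetes stratum only would attract attention. With strata this small, such a pattern arises often when the true effect is the same in both.

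**Working it through.** **Inputs from section 2.6.1.** "final mean MNSI questionnaire of 5.3 ± 2.5 compared to 7.1 ± 2.8 in the control group" gives a difference of 7.1 − 5.3 = 1.8 points. The root-mean-square SD is √((2.5² + 2.8²)/2) = 2.654. About 60 participants are to be evaluable and about 70 enrolled, 1:1, with 14% loss.

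**Assumptions.** Tests are two-sided at 0.05; the article prints alpha as 0.5, which is a separate matter. Subgroup shares of 50%, one third and 20% are assumed, since the article gives none for this trial. Its background rates in the Introduction (up to 14.2% diabetes before diagnosis, up to 65% needing steroids) are wider than this range.

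**The plan's own figure.** With alpha 0.05 two-sided, 80% power and a single SD of 2.5, the normal formula gives 31 per arm, 62 in all, close to the stated 60. With SD 2.654 it gives 35 per arm, 70 evaluable. Then 60/(1 − 0.14) = 69.8, so 70 enrolled. These figures concern the overall comparison; the article gives none for subgroups.

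**Step 1: what adjustment returns.** A linear model with main effects only was simulated with 60 participants, a 47% subgroup share and 3,000 runs per scenario.

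| True effect outside / inside the subgroup | Mean diet coefficient (reduction, points) | Interaction test rejects |
|---|---|---|
| 1.8 / 1.8 | 1.79 | 5% |
| 0.9 / 2.7 | 1.76 | 26% |
| 0 / 3.6 | 1.69 | 72% |

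The coefficient is close to the share-weighted average, for example 0.53 × 0 + 0.47 × 3.6 = 1.69. It barely moves while the subgroup effects go from equal to entirely one-sided. A logistic model without a product term has the same limitation, in that it also contains one diet coefficient.

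**Step 2: what stratum-by-stratum tests return when the effect is the same.** Power in each stratum comes from the noncentral t distribution with n per arm and noncentrality 1.8/(2.654 × √(2/n)). With stratum powers pa and pb, P(exactly one significant) = pa(1 − pb) + pb(1 − pa).

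| Smaller stratum's share | n per arm | Power in each | Exactly one significant | Only the smaller stratum |
|---|---|---|---|---|
| 50% | 15 and 15 | 0.434, 0.434 | 0.434 × 0.566 × 2 = 49% | 25% (either one named in advance) |
| one third | 10 and 20 | 0.300, 0.552 | 0.300 × 0.448 + 0.552 × 0.700 = 52% | 0.300 × 0.448 = 13% |
| 20% | 6 and 24 | 0.186, 0.633 | 0.186 × 0.367 + 0.633 × 0.814 = 58% | 0.186 × 0.367 = 7% |

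**Step 3: what an interaction term could deliver.** SE = 2.654 × √(2/na + 2/nb), where na and nb are the numbers per arm in the two strata; the half-width is 1.96 × SE.

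| n per arm | SE | 95% half-width | Power for a 1.8-point interaction |
|---|---|---|---|
| 15 and 15 | 1.37 | ±2.7 | 26% |
| 10 and 20 | 1.45 | ±2.8 | 24% |
| 6 and 24 | 1.71 | ±3.4 | 18% |

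These are before any gain from adjusting for the baseline score.

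**The case against.** The strongest reply is that this is a condensed article and that model terms usually belong in the analysis plan. The subgroup wording is loose enough to accommodate interaction terms, and stratified estimates with intervals are legitimate description. That is fair as far as silence goes. What remains is that section 2.6.2 does not merely leave a term out. It states a method, adjustment, for a stated purpose, effects in sub-populations, and the two do not match. It also names two post-randomisation variables as modifiers.

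Several stronger readings are tempting and are not supported:

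- **That p-values will be compared across strata.** A reader might infer this from the stratification and the t-tests, but the article does not say so.
- **That a finding confined to people with diabetes is likely by chance.** The 49% to 58% counts a lone significant result in either stratum. The lone result falls in the diabetic stratum in about 25%, 13% and 7% of trials when people with diabetes are 50%, one third and 20% of the sample. Where they are a minority, the opposite artefact is the more common one.
- **That diabetes and steroid use are the effect modifiers being adjusted for.** Diabetes is in the covariate list, and steroid use is not in the model.
- **That effect modification is the trial's main question.** The objectives in section 2.2 are the overall diet effect, then tolerability and side effects.

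It is also true that an interaction test is weak at this size. That limits what the remedy can show, but it does not make stratum-by-stratum reading any sounder.

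**Conclusion.** The point holds in a limited form. As written, neither the adjusted regression nor the stratified outcomes can tell whether the diet effect differs by diabetes status or steroid use, and the modifiers named in section 2.6.2 may be consequences of the diet. With an identical 1.8-point effect in both strata, a significant result in exactly one of them is roughly an even chance (49% to 58%), so such a pattern would say little about a real difference.

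The size rests on 60 evaluable participants, SD 2.65, two-sided 0.05 and assumed subgroup shares of 20% to 50%. The logical point depends on none of these. The importance is minor to moderate: the overall treatment comparison is untouched, and no confirmatory subgroup claim is stated.

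**What to change.** For each continuous outcome, specify one linear model with treatment, baseline score, baseline diabetes status, baseline steroid use, and the treatment-by-diabetes and treatment-by-steroid terms. Then:

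- report each interaction estimate with its 95% confidence interval, labelled exploratory;
- state the expected precision in advance, about ±2.7 to ±3.4 MNSI points before baseline adjustment;
- make no efficacy claim from a single stratum;
- define subgroups only by variables measured before randomisation, and do not use weight change or medication de-escalation as subgroup factors or as adjustment variables in this model.

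**Cost.** No new data, visits or participants are needed. It is more than one extra term, because a linear model takes the place of the logistic one for the continuous scores. The interaction test will have only about 18% to 26% power for a difference as large as the whole planned effect, so it will seldom settle the question. It will show honestly how much remains uncertain.
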